## Abstract

**Background:**

Previous research has shown that electroacupuncture therapy has a potential therapeutic effect for simple female stress urinary incontinence. In this study, pelvic floor muscle training, the first-line treatment for stress urinary incontinence in women based on meta-analysis of numerous randomized control trials and recommended by international clinical practice, is used as a control group to demonstrate whether electroacupuncture therapy is a better method for female stress urinary incontinence.

**Methods/design:**

A randomized controlled trial has been designed to evaluate the therapeutic benefit of electroacupuncture for female stress urinary incontinence compared with pelvic floor muscle training. The safety of electroacupuncture and patient compliance will also be evaluated. Untoward reaction to the electroacupuncture, including a broken needle, fainting on acupuncture, or pain during acupuncture, will be recorded and the therapy will be stopped if an untoward reaction occurs. After we have received full ethical approval and patient consent, participants will be randomized to receive a series of 24 electroacupuncture or pelvic floor muscle training interventions. The frequency and amount of leakage will be measured as the primary outcome parameters. Secondary outcome parameters include the 1-hour pad test, the short-form of the International Consultation on Incontinence Questionnaire, patient subjective effectiveness evaluation, weekly usage of pad, and usage of specialty therapy for female stress urinary incontinence.

**Discussion:**

This trial will help to determine whether electroacupuncture is a more effective treatment than pelvic floor muscle training for patients with female stress urinary incontinence.

**Trial registration:**

ClinicalTrials.gov NCT01940432 (12 September 2013).

**Electronic supplementary material:**

The online version of this article (doi:10.1186/s13063-015-0560-1) contains supplementary material, which is available to authorized users.

## Background

According to the International Continence Society, stress urinary incontinence (SUI) [1] is defined as involuntary loss of urine during coughing or sneezing [2]. Female SUI (FSUI) is a common condition which affects quality of life in women aged 40 to 75 years [3] (Figure 1).

**Figure 1 Fig1:**
[figure not shown]
**Trial design.**

In China, the prevalence of urinary incontinence in women is 46.5%, of which SUI makes up 59.6% [4]. Any women of old age are at high risk of SUI [5]. Women with SUI are embarrassed to take part in social activities, and as a result their lifestyles are altered putting them at increased risk of lifestyle-related disease, such as osteoporosis, obesity, diabetes, hypertension, coronary disease, mammary cancer, carcinoma of colon, depression, anxiety, and so forth [6].

The International Consultation on Urological Diseases recommend that treatment methods for mild and moderate SUI are lifestyle intervention, behavior therapy, pelvic floor muscle (PFM) training, functional electroacupuncture, and so forth [7]. PFM training has level A evidence of efficacy, with a curative rate ranging from 30 to 60% [8]. However, training duration should be at least 2 months. In China, PFM training is not as efficient as expected because there are not enough physical therapists, and patient compliance to treatment needs to be improved [9]. Primary therapy for moderate and severe SUI is surgery, which carries a high potential for adverse events. A safety communication from the US Food and Drug Administration on serious complications associated with transvaginal placement of a surgical mesh for pelvic organ prolapse was issued on 13 July 2011 [10]. Therefore, there is a need to explore other treatment avenues.

By contrast, acupuncture for FSUI works over a short period with a high curative rate [11], which shows potential advantages for FSUI. In a previous study [12], electroacupunture was verified as a more effective therapy for SUI than acupuncture, possibly related to the PFM and nerves. However, the level of evidence was rated as “low” [12].

A trial of high methodological quality is needed to determine whether electroacupuncture is effective for FSUI. This trial will evaluate the effect of electroacupuncture and investigate whether electroacupuncture is a better treatment for FSUI than PFM training.

## Methods/design

### Design

This study is a double-blind, multicenter, randomized controlled trial using two study arms: an electroacupuncture group and a PFM training group.

After consent, participants will be allocated to either group (the electroacupuncture group or the PFM training group) using computer generated randomization lists. Block randomization was chosen to allow for equal numbers in each group at regular time intervals. These participants will be randomly assigned to the two groups through central randomization in a 1:1 ratio. The central randomization system will be used and performed by the Clinical Evaluation Center at the China Academy of Chinese Medical Sciences in Beijing. A random number and group assignment will be immediately received by telephone, mobile phone, or website sent from the Clinical Evaluation Center. Participants will receive 24 sessions of electroacupuncture or PFM training over 8 weeks at a frequency of three times per week.

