### Biases

Our research is a randomized controlled trial, which is the best way to avoid selection bias, and the Clinical Evaluation Center of China Academy of Traditional Chinese Medical Sciences is responsible for the central randomization system. All of the parameters will be sealed to ensure a randomized controlled trial by removing human interference. The patient, evaluator, and statistical clerk will be blinded. Patients will be blinded to the other intervention.

Strict restrictions on inclusion criteria will be applied, and specific inclusion and exclusion criteria will restrict participants to a particular range to reduce differences between patients, making the conclusions more valid.

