### Interventions

#### Electroacupuncture

The participants will be treated continuously for 8 weeks, three times per week on alternate days for 30 minutes per session, giving 24 treatments in total. The procedure is as follows. Electroacupuncture on the points Bilateral Zhong Liao (BL33) and Hui Yang (BL35) (Additional file 1) for 50 to 60 mm (using a 75-mm filiform needle). The needle will be inserted inward and downward at an angle of 30 to 45°. After insertion, the needle will be twirled, lifted and thrust three times until the patient has a needling sensation If the needle breaks during treatment it will be removed and the quality of the other needles will be checked. If a patient faints, the treatment will be suspended until they recover. If a patient feels pain, we will change the needle insertion angle and depth. The electric stimulator is applied to bilateral BL33 and BL35 with a continuous wave, 50 Hz electric current at 1 to 5 mA from the positive pole to the negative pole. The treatment design is based on literature research over the preceding 10 years, former research results and expert consensus.

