#### Pelvic floor muscle training

The participants are treated continuously for 8 weeks, three times a week on alternate days, giving 24 treatments in total (Additional file 2). Before performing PFM training, patients should learn the position of the PFM. The PFM is the muscle we contract to stop passing water when urinating. Alternatively, vaginal palpation can be used to identify the specific position of the PFM. The patient can insert their finger into the vagina to feel the muscle contraction if convenient. PFM training is performed by standing/sitting/lying on the back with knees bent. Continuously contract the PFM three times, until the patient feels they cannot contract any more strongly; then hold on the contraction, and breathe twice (inhale, exhale, inhale, exhale); then relax the whole body, breathing another two times (inhale, exhale, inhale, exhale). Then contract PFM again. Repeat the above procedure for 15 minutes [14].

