### Outcome measures

#### Primary outcome measures

Difference in mean frequency of leakage over 24 hours based on a 72-hour diary (Additional file 3) compared with baseline. The mean frequency of leakage over a 24-hour period is calculated from the 72-hour voiding diaries, measured four times, in weeks 2, 4, 6 and 8. This mean frequency is compared with the baseline frequency measured at week 0.Difference in mean degrees of leakage over 24 hours based on a 72-hour diary, compared with the baseline. The mean quantity of fluid loss over a mean of 24 hours is calculated from the 72-hour voiding diary, measured three times, in weeks 2, 4, 6 and 8. This mean degree of leakage is compared with the baseline mean degree measured at week 0. The degree can be divided into four levels: mild degree (a very small amount of leakage with several drops); moderate degree (moderate leakage which wets the women’s underwear, but does not wet the over-trousers); and severe degree (a large amount of leakage which wet the over-trousers)A severity index for FSUI: frequency of leakage × amount of leakage, comparing the value of weeks 2, 4, 6 and 8 with baseline (0 week).

Scoring for frequency of leakage is defined as: 1 = less than once per month; 2 = several times per month; 3 = several times per week; 4 = every day or night.

Scoring for amount of leakage is defined as: 1 = a few drops; 2 = small splashes; 3 = more than small splashes.

Giving a severity index of: mild = 1–2; moderate = 3–6; severe = 8–9; very severe = 12. [15].

All of the primary outcome measures are based on a 72-hour diary. Every 2 weeks, patients will be asked to record the amount of fluid they drink (tea, coffee, milk, water and so forth) and leakage information (what movement they were doing when the leakage happened) for 3 consecutive days. Researchers will calculate the above primary outcome measures according to the patient’s record.

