In conclusion, the results of this trial are expected to confirm the effectiveness of electroacupuncture and whether it is a better treatment for SUI compared with PFM training.

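### The trial is labelled double-blind with patients blinded, but patients know their treatment and supply every primary outcome, so evaluator and statistician blinding cannot protect those outcomes from reporting bias

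*Protocol article*

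**What the plan says.** The Design section states: "This study is a double-blind, multicenter, randomized controlled trial using two study arms". The Biases section adds: "The patient, evaluator, and statistical clerk will be blinded. Patients will be blinded to the other intervention".

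The two treatments are described under Interventions. For electroacupuncture, "the needle will be twirled, lifted and thrust three times until the patient has a needling sensation", and a current is then applied. In the control arm, "PFM training is performed by standing/sitting/lying on the back with knees bent", and the patient repeats the contractions for 15 minutes. Neither description includes a sham procedure or a double-dummy.

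On the outcomes, the Primary outcome measures section says: "All of the primary outcome measures are based on a 72-hour diary". The patient keeps the record and the researchers compute the outcomes from it. The 1-hour pad test appears under Secondary outcome measures, at 8, 20 and 32 weeks. Data analysis provides for a statistician blinded to allocation. The article closes by saying that "the results of this trial are expected to confirm the effectiveness of electroacupuncture and whether it is a better treatment for SUI".

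**The concern.** A patient who is needled until she feels a sensation, and one who is taught to contract a muscle, each know what they are receiving. The article nevertheless states that patients are blinded and puts the double-blind label on the design.

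The error matters because of who measures the primary outcomes. If an independent evaluator took them, evaluator blinding would do most of the work even with unblinded patients. Here the patient is in effect the assessor of leak frequency and leak degree, and the severity index is the product of a frequency score and an amount score. Any difference between arms in how readily women notice, count or grade leaks passes straight into the treatment comparison.

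The label also has consequences for readers. The Discussion criticises earlier studies for uncertain blinding, links this to their low evidence grade, and presents this trial as the better one. A reader who trusts the label would treat a diary-based difference as protected against a bias to which it is open.

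**Working it through.** **Passages side by side (Protocol article)**

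1. Design: the trial is double-blind.
2. Biases: "The patient, evaluator, and statistical clerk will be blinded". The next sentence gives the meaning: "Patients will be blinded to the other intervention". Being uninformed about the other arm is a different property from not knowing one's own arm, and only the second is blinding to allocation.
3. Electroacupuncture and Pelvic floor muscle training: the treatments differ visibly and physically, with no masking device. It follows from 1 to 3 that patients are not blinded.
4. Primary outcome measures: all three outcomes derive from the diary, and researchers only calculate from it. It follows that evaluator blinding acts after the data have been produced.
5. Data analysis: the statistician is blinded. This guards analytic choices and leaves diary entries as they were written.

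**Illustration of what a reporting shift could do**

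The blinding statement has no figure of its own to reproduce. The Sample size section supplies what is needed for scale, but the shift itself is assumed.

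Inputs from Sample size:
- Electroacupuncture reduction: 95% CI 1.52 to 3.34, midpoint (1.52 + 3.34)/2 = 2.43.
- PFM reduction: 1.5, SD 1.1.
- Difference: 2.43 − 1.5 = 0.93. The article does not state this value; it is derived here.
- Power 90%, alpha 0.05 (taken as two-sided), drop-out 20%, total 320.
- Completers per arm: 320 × 0.8 / 2 = 128.

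The stated inputs do not reproduce 320. With difference 0.93 and SD 1.1, n per arm = 2 × 3.2415² × 1.1² / 0.93² ≈ 29.4, so 30. Then 30/0.8 = 37.5, so 38 per arm and 76 in total. The SD for the electroacupuncture arm is not given. That is a separate matter, but it is why two standard errors are shown:

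- (a) SE implied by 90% power for 0.93: 0.93/3.2415 = 0.287. With 128 per arm this corresponds to an SD of about 2.30.
- (b) SE from the stated SD: 1.1 × √(2/128) = 1.1 × 0.125 = 0.1375.

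With no true difference and a reporting shift b towards electroacupuncture, the chance of a significant two-sided result is Φ(b/SE − 1.96) + Φ(−b/SE − 1.96).

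| Assumed shift b (leaks/day) | (a) SE 0.287 | (b) SE 0.1375 |
|---|---|---|
| 0 | 5% | 5% |
| 0.2 | 10.8% | 30.7% |
| 0.3 | 18.2% | 58.8% |
| 0.5 | about 41% | 95.3% |

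For b = 0.3: (a) 0.3/0.287 = 1.05, so Φ(−0.91) ≈ 0.18; (b) 0.3/0.1375 = 2.18, so Φ(0.22) ≈ 0.59. A shift of 0.3 is about a third of the 0.93 difference (0.3/0.93 = 0.32).

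**The case against.** The strongest reply is that unblinded patients are inherent in comparing needling with exercise, that the stated question is comparative and an active-comparator trial answers it without a sham, and that the Biases section itself discloses what it means by patient blinding. Much of this stands. The design is legitimate, and asking for a sham or untreated arm would be a preference. The disclosure does not rescue the text, because it follows directly on a sentence that lists the patient as blinded and sits beneath a double-blind label.

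A reader might infer more than the document supports, in four ways.

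- *That the trial has no protection against bias.* It has central randomization run by the Clinical Evaluation Center, a statistician blinded to allocation, and a blinded evaluator for whatever the evaluator measures. Only patient blinding fails, and with it the protection of the diary outcomes.
- *That the bias favours electroacupuncture.* The Background speaks of a high curative rate for acupuncture and of disappointing PFM results in China, but the article also presents PFM training as first-line with level A evidence. Both arms are recruited and treated in the same departments, so the setting does not separate them. The direction is not established.
- *That the error rate will be 18% or 59%.* The shift is assumed, and the choice of SE alone moves the result threefold.
- *That a null result would count specially against the plan.* Failure to show effectiveness from a null result is common to superiority trials and has nothing to do with blinding.

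**Conclusion.** The point holds in this form. The article states a property, patient blinding, that its own intervention descriptions rule out, and the loss of that property reaches all three primary outcomes. This is a wrong statement in the text and does not depend on anything a fuller protocol or analysis plan might add. It should be corrected.

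The conclusion rests on the passages and not on the arithmetic. The figures of about 18% and about 59% at 0.3 leaks per day show only that a modest reporting shift could matter. They assume no true difference, a shift towards one arm, two-sided testing at 0.05, a normal approximation and, for the second, 128 completers per arm. The documents give neither the size nor the direction of any shift. It would be unsupported to conclude that a significant diary result must be an artefact, or that the trial cannot answer its comparative question.

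**What to change.** 1. **Design section.** Replace the double-blind label with: open to patients and therapists, with blinded outcome evaluator and statistician.
2. **Biases section.** Take the patient out of the list of those blinded, delete "Patients will be blinded to the other intervention", and add a sentence acknowledging the risk of reporting bias in the diary outcomes.
3. **Outcome sections.** Name the week-8 1-hour pad test as the key supportive outcome and state that the blinded evaluator measures it. The test is already scheduled and already heads the list of secondary outcomes, but the article does not say who measures it or give it a role in the conclusion. Require its between-group estimate and confidence interval to be reported beside any superiority conclusion drawn from the diary.
4. **Closing conclusion.** Limit it to electroacupuncture versus this PFM programme, in place of confirming effectiveness in general.

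These changes need no new arm, visit or measurement; they need wording and an assurance about who takes the pad test. They do not remove reporting bias from the diary, which stays primary. They make the claim match the design and put a weighed measure next to it. The price is a less favourable design label and a narrower claim.

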### Ethics

This study is performed in accordance with the principles of the Declaration of Helsinki [13], and has been approved by the ethics committee boards of the participating hospitals (Shaanxi Hospital of Traditional Chinese Medicine, Yueyang Hospital of Integrated Traditional Chinese and Western Medicine affiliated to Shanghai University of Traditional Chinese Medicine, The First Hospital of Hunan University of Chinese Medicine, Anhui Hospital of Acupuncture and Moxibustion, Nanjing Hospital of Traditional Chinese Medicine, Xi’an hospital of Traditional Chinese Medicine). Written informed consent will be obtained from each subject before the patient enters the trial.

### Biases

Our research is a randomized controlled trial, which is the best way to avoid selection bias, and the Clinical Evaluation Center of China Academy of Traditional Chinese Medical Sciences is responsible for the central randomization system. All of the parameters will be sealed to ensure a randomized controlled trial by removing human interference. The patient, evaluator, and statistical clerk will be blinded. Patients will be blinded to the other intervention.

Strict restrictions on inclusion criteria will be applied, and specific inclusion and exclusion criteria will restrict participants to a particular range to reduce differences between patients, making the conclusions more valid.

### Participants

Patients will be recruited and treated at the Acupuncture and Moxibustion Department in Shaanxi Hospital of Traditional Chinese Medicine and the other five co-operative hospitals of Yueyang Hospital of Integrated Traditional Chinese and Western Medicine and Shanghai University of Traditional Chinese Medicine, Anhui Hospital of Traditional Chinese Medicine, The First Hospital of Hunan University of Chinese Medicine, Nanjing Hospital of Traditional Chinese Medicine and Xi’an hospital of Traditional Chinese Medicine.

Patients will be eligible if they satisfy the following criteria:Aged 40 to 75 years.Female.Meet the diagnosis of simple FSUI (urine leakage associated with increased abdominal pressure from laughing, sneezing, coughing, climbing stairs, or other physical stressors on the abdominal cavity and, thus, the bladder). Also, the amount of urine loss should be greater than 1 g using the 1-hour pad test.Volunteered to join this research and signed the informed consent.

Potential participants will be excluded if they have any of the following:Urge urinary incontinence (involuntary leakage accompanied by or immediately preceded by urgency), mixed urinary incontinence (a combination of stress and urge incontinence, marked by involuntary leakage associated with urgency and also with exertion, effort, sneezing, or coughing), overflow urinary incontinence, and so forth.Operation for urinary incontinence or a pelvic floor operation.Greater than second-degree prolapse.Symptomatic urinary tract infection.Greater than 30 ml residual urinary volume.Less than 20 ml/second maximum urinary flow rateConstrained movement of walking, climbing stairs, running.Continuous treatment for SUI or receiving medicine for bladder function.Serious cardiovascular, cerebral, liver, kidney, or psychiatric disease, diabetes, Multiple System Atrophy, injury of cauda equine, myelopathy.Pregnancy or undergoing lactation.A cardiac pacemaker, metal allergy or severe needle phobia.

### Interventions

#### Electroacupuncture

The participants will be treated continuously for 8 weeks, three times per week on alternate days for 30 minutes per session, giving 24 treatments in total. The procedure is as follows. Electroacupuncture on the points Bilateral Zhong Liao (BL33) and Hui Yang (BL35) (Additional file 1) for 50 to 60 mm (using a 75-mm filiform needle). The needle will be inserted inward and downward at an angle of 30 to 45°. After insertion, the needle will be twirled, lifted and thrust three times until the patient has a needling sensation If the needle breaks during treatment it will be removed and the quality of the other needles will be checked. If a patient faints, the treatment will be suspended until they recover. If a patient feels pain, we will change the needle insertion angle and depth. The electric stimulator is applied to bilateral BL33 and BL35 with a continuous wave, 50 Hz electric current at 1 to 5 mA from the positive pole to the negative pole. The treatment design is based on literature research over the preceding 10 years, former research results and expert consensus.

#### Pelvic floor muscle training

The participants are treated continuously for 8 weeks, three times a week on alternate days, giving 24 treatments in total (Additional file 2). Before performing PFM training, patients should learn the position of the PFM. The PFM is the muscle we contract to stop passing water when urinating. Alternatively, vaginal palpation can be used to identify the specific position of the PFM. The patient can insert their finger into the vagina to feel the muscle contraction if convenient. PFM training is performed by standing/sitting/lying on the back with knees bent. Continuously contract the PFM three times, until the patient feels they cannot contract any more strongly; then hold on the contraction, and breathe twice (inhale, exhale, inhale, exhale); then relax the whole body, breathing another two times (inhale, exhale, inhale, exhale). Then contract PFM again. Repeat the above procedure for 15 minutes [14].

